##### Other

Depressive symptoms will be measured with the Calgary Depression Scale for Schizophrenia (CDS-C) [47], an observer-rated Likert-scale to measure depressive symptoms (Cronbach’s alpha=0.80; inter-rater reliability Kappa coefficient > 0.79; test-retest reliability r=0.927), the Simpson-Angus Rating Scale (SAS) [48], the Barnes Akathisia Rating Scale (BARS), and the Abnormal Involuntary Movement Scale (AIMS). Participants’ IQs will be collected from medical records (if available) and the Mini-MMSE will be used to verify each participant’s capacity to participate in the study. If, at baseline, it is obvious that the participant suffers from a condition that will interfere with participation in the study (IQ, MMSE), the participant will be excluded from the study. Permission to use each instrument has been obtained and license costs have been paid as necessary.

#### Neurocognition

##### Electroencephalography (EEG)

The impact of gaming on brain functional networks and changes in neuronal dynamics can be revealed by an EEG during the execution of a visual working memory task. Resting-state EEG will be collected to evaluate changes in spontaneous activities in the brain for comparison with the resting-state MRI. The EEG has been extensively utilised to assess the effectiveness of daily cognitive exercises to improve sensory information processing, from attention to working memory processes, in people with schizophrenia. Its superior temporal resolution is most apt in identifying relevant markers in neuronal network dynamics that underlie the observed improvement, that might help in further identifying subsets of patients most likely to benefit from cognitive exercises [49].

##### Resting-state fMRI

In resting-state functional (rsfMRI) and structural MRIs, the most often reported neurocognition measurement for regions includes that of the nucleus accumbens, amygdala, striatum, anterior cingulate cortex, orbitofrontal cortex, and dorsolateral prefrontal cortex [50], the dorsal lateral prefrontal cortex and the anterior cingulate Testgyrus [51]. During the rsfMRI, the subject will not perform any tasks while being scanned. The rsfMRI is based on the principle that, even when the brain is at rest, there are still low fluctuations of neural activity. While the resting-state neural activity is at a much lower rate than when the brain is active, it can be used as a biomarker to study the underlying neuronal networks.

Comparing pre- and post-training records will reveal the impact of cognitive training with computerised exercises on the neuronal networks underlying the physiological basis of working memory ability. We will assess how the training influences inter-areal functional and structural (measured with MRI/Diffusion tensor imaging [DTI]) connectivity and the quantitative indices of cortical criticality and excitation/inhibition balance.

### Data collection and follow-up

To avoid burdening the patients, data will be collected in separate phases (see Table 1):
A preparatory data collection (estimated 45 min) will be collected only once, at the beginning of the study. It aims to collate the background information of the participants to determine their capacity for informed consent and any other potential factors that might restrict participation in the intervention (background information, IQ, medication dosage [based on medical records], MMSE, CDS-C, SAS, BARS, AIMS).2)For the primary (verbal working memory) and secondary outcomes (estimated 75 min) (cognitive and social functioning, experience of pleasure, self-efficacy, negative symptoms), the data will be collected at three points in time: at baseline, after the intervention (3-month follow up) and at a six-month follow-up (6 months after baseline).3)The EEG measures taken during the working memory test will be collected at baseline and 3 months after baseline only (EEG 1 h; rsfMRI and structural MRI, 45 min).

**Table 1 Tab1:** Instruments and study stages

TIME POINTS Instruments	Eligibility screening	Preparatory data	Baseline	Allocation	Intervention	3 month follow-up	6 month follow-up
Inclusion/exclusion criteria	**X**						
Background information		**X**					
IQ (from medical records if available)		**X**					
Current medication dosage		**X**					
Computer use		**X**					
MMSE		**X**					
Calgary Depression Scale for Schizophrenia, CDS-C		**X**					
Simpson-Angus Rating Scale, SAS		**X**					
Barnes Akathisia Rating Scale, BARS		**X**					
Abnormal Movement Involuntary Scale, AIMS		**X**					
**Primary and secondary outcomes**							
Letter-Number-Span-Test, LNST			**X**			**X**	**X**
Trail Making Test, TMT			**X**			**X**	**X**
Sustained Attention to Response Task, SART			**X**			**X**	**X**
Spatial Span			**X**			**X**	**X**
Wisconsin Card Sorting			**X**			**X**	**X**
Brief Social Phobia Scale, BSPS			**X**			**X**	**X**
Temporal Experience of Pleasure Scale, TEPS			**X**			**X**	**X**
General Self-efficacy Scale, GSE			**X**			**X**	**X**
Clinical Assessment for Negative Symptoms, CAINS			**X**			**X**	**X**
EEG^a^			**X**			**X**	
MRI^b^			**X**			**X**	
ACP^c^				**X**			
**Study groups**							
Cognitive training with computerized exercises (experiment group)					X		
Entertainment video gaming (active control group)					X		
TAU (passive control group)							

^a^Convenience sample; ^b^Randomised subsample; ^c^ACP test planned but need to discontinue due to technological problems of the measure

First, for the primary and secondary outcomes (cognitive and social functioning, experience of pleasure, self-efficacy, negative symptoms), the data will be collected in paper format or digital format [5] by a trained psychologist or RA.

Second, the EEG will be recorded during resting state and a multi-objects visual working memory task (VWM). The task, modified from our prior studies [52], will be performed so that the neuronal mechanisms limiting VWM performance and capacity can be identified during the memory retention period. Subjects will attend either hemifield, depending on the pre-stimulus cue, and memorise a visual display containing one to six objects. After the retention period, a second stimulus will appear, and the subject will answer whether the stimulus presented in the second display matches part of the first display or not. We will correlate both local and large-scale neuronal dynamics with the task performance, both in pre-training and post-training neuroimaging sessions.

Third, fMRI scans will be acquired using a Philips 3 T MRI scanner. During scanning, a painless procedure, patients will rest on a table, which will be slid into a large tunnel-shaped scanner. As there will be a constant drumming noise during scanning, earplugs or earphones will be provided. During the examination, the patient will be able to freely communicate with staff via an intercom. Resting-state fMRI data will be acquired using T2-weighted echo planar pulse sequence imaging (300 whole-brain volumes were collected with slice thickness=4 mm, TE=30 ms, TR= 2000 ms, flip angle=90 degrees, spatial resolution 3x3x4 mm isotropic voxels, transverse orientation, 32 slices fully covering the cerebral cortex and the cerebellum, acquisition time = 10 min). Structural MRIs will be acquired with the MP-RAGE T1 sequence. A DTI of the axonal tracts in cerebral white matter will be performed with a protocol validated in the Human Connectome Project. We will acquire a 15-min session of resting-state data to obtain high-quality measurements of intrinsic functional connectivity of BOLD signals (fMRI) [53] and critical dynamics (fMRI) [54].

### Data analysis

#### Cognitive and clinical outcomes

The demographic information and outcome measurements of the participants in the three study groups will be compared for similarities at baseline. Based on the types of variables, Chi Square tests and analyses of variance (ANOVA) will be used for categorical and continuous variables, respectively. Variables found significantly different between study groups will be controlled in the main analysis as covariates. The normality assumption of the outcome scores will be tested (Kolmogorov-Simonov tests). Outcome measures of non-normal distribution will be transformed to normal in the main analysis.

In the main analysis, we will estimate and test efficacy of interventions on the primary and secondary outcomes. Based on the intention-to-treat principle, we will first assess intervention effects on the primary outcome, verbal working memory, by means of multilevel modelling analysis. A two-level model can be built with repeated time points at level 1, and patients at level 2. Two indicator variables, G2 and G3, will be included in the fixed part of the model to estimate and test mean differences between the cognitive training group with computerised exercises (G1) and the entertainment gaming group (G2), as well as between G1 and the non-gaming control group (G3). The baseline difference between G2 and G3 can be tested using a Ward test, based on the regression coefficient estimates of the two indicators. For changes in the outcome over time, two more indicators, variables T2 and T3, in contrast to the baseline time point, T1, will be included in the fixed part of the model to estimate changes from baseline to 3 months, and from baseline to 6 months. To assess the effects of interventions over time, interaction terms between the treatment group indicators, G2 and G3, and time indicators, T2 and T3, will be included in the fixed part of the model. The significantly different demographics between groups identified in the first step of the analysis and other possible confounders will be adjusted by including them in the main effect model. The within-patient random effects of the outcome measurements will naturally be taken into account by the level two variance in the model. A pairwise comparison and other hypotheses on the intervention effects can be tested using a generalised Ward test with an adequate degree of freedom from the modelling analysis. This analysis approach has two main advantages: a statistically highly efficiency and taking missing data into account. The effects of interventions on other secondary outcome measures, normally distributed and measured at three time points, such as patients’ cognitive and social functioning, experience of pleasure, and self-efficacy, will be analysed using the same model, but a separate model for each outcome. A multilevel logistic model will be used for outcomes in binary form, and multilevel multinomial models will be used for ordinal or nominal outcomes. For outcomes measured at two time points only, such as neurocognitive outcomes, the model will have only one time indicator with two interaction terms to test the efficacy of cognitive training with computerised exercises three months into the trial.

SPSS (the Statistical Package for the Social Sciences) Missing Values will be used to identify the amount and pattern of missing data. If missing values are few and randomly allocated, the last observation carried forward (LOCF) will be used to replace the missing data. If missing values are not randomly distributed, multiple imputation approaches will be used. A sensitivity analysis will be performed by comparing results from analysis datasets without missing data imputation and with imputation.

In all tests, significant differences between groups will be detected with a 95% confidence level, and *P* values of < 0.05 will be considered significant. Statistical analyses will be carried out with SAS System for Windows, version 9.4 (SAS Institute Inc.) or R statistical software (R Core Team, 2016).

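### Covariates are chosen by baseline significance tests and entered as main effects that barely act on the group-by-time contrasts, and a normality test on raw scores triggers an unnamed transformation of the primary outcome

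*Protocol article*

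**What the plan says.** All the rules are in the protocol article, Data analysis, Cognitive and clinical outcomes.

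- **Screening.** "The demographic information and outcome measurements of the participants in the three study groups will be compared for similarities at baseline", by chi-square tests or ANOVA, and "Variables found significantly different between study groups will be controlled in the main analysis as covariates".
- **Entry into the model.** The paragraph on the main analysis returns to this with a narrower scope, "The significantly different demographics between groups identified in the first step of the analysis", and adds an open category: "other possible confounders will be adjusted by including them in the main effect model". No covariate-by-time term is described.
- **Model and treatment effect.** "A two-level model can be built with repeated time points at level 1, and patients at level 2". The baseline score is one of the three responses. Efficacy rests on the following: "interaction terms between the treatment group indicators, G2 and G3, and time indicators, T2 and T3, will be included in the fixed part".
- **Normality.** "The normality assumption of the outcome scores will be tested" by a Kolmogorov-Smirnov test (misspelt in the text), and "Outcome measures of non-normal distribution will be transformed to normal in the main analysis". No transformation or back-transformation is named.

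**The concern.** Arms are allocated from computer-generated random numbers in blocks of six (Randomisation, allocation concealment and blinding), so under sound randomisation a significant baseline difference is a chance event. Selecting on it picks variables for their imbalance and not for their relation to outcome. The open category of other confounders also leaves the primary model to be settled after data are seen.

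The form of adjustment then does not match the treatment contrast. Efficacy is a difference in change from baseline, and a covariate that shifts a patient's scores equally at all three visits drops out of that change.

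The two statements of scope differ. The first covers variables that include outcome measurements; the second covers demographics. On the first reading, baseline LNST could be both a covariate and the T1 response.

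Finally, the model's distributional assumption concerns residuals and random effects, not the marginal scores. A test on the scores that automatically changes the scale lets the data choose the units in which the primary effect is reported.

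**Working it through.** **Inputs from the article.** Effect size 0.58, power 0.80, adjusted alpha 0.01274, 66 per group at follow-up and 16% dropout (Power analysis and sample size); 78 per group allocated (Interventions); significance at 0.05 (end of Cognitive and clinical outcomes). **Assumed, because not given:** within-patient correlation ρ, covariate imbalance of 0.4 SD, covariate-outcome correlation of 0.3 to 0.5, number of screened variables k, and SD of the LNST score.

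**1. The plan's own figure.** Alpha = 1 − 0.95^(1/4) = 0.01274. n = 2(0.842 + 2.491)² / 0.58² = 66.03 per group, against the stated 66. It reproduces, and the point does not dispute it.

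**2. How often screening flags something by chance.** For k independent variables the probability is 1 − 0.95^k: 23% (k = 5), 40% (k = 10), 54% (k = 15), 64% (k = 20).

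**3. Effect of a main-effect covariate, complete data.** In a random-intercept model with everyone seen at all three times, each interaction equals a difference between arms in mean change. A term constant within patient cancels from every change. With outcome SD 1, the standard error is √[2(1 − ρ) × 2/n]. For n = 78:

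- ρ = 0.5: √(2/78) = 0.160
- ρ = 0.7: √(1.2/78) = 0.124

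Neither value depends on the covariate. Simulation agrees: with the 0.4 SD imbalance, the four interactions changed by less than 10⁻¹³ SD and the ratio of standard errors was 1.000.

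**4. The same with dropout.** With 16% covariate-dependent dropout, the mean absolute change was 0.004 to 0.013 SD and the largest in any replicate was 0.056, against standard errors of 0.13 to 0.17. The standard error fell by at most 0.5%. Where gaps are filled by last observation carried forward, as the article allows when they are few and random, the data are complete again and step 3 applies.

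**5. What explicit baseline adjustment would give.** The variance of change is proportional to 2(1 − ρ), and that of a baseline-adjusted follow-up score to 1 − ρ². The ratio of standard errors is √[(1 + ρ)/2]:

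| ρ (assumed) | SE ratio | Reduction |
|---|---|---|
| 0.5 | 0.87 | 13% |
| 0.6 | 0.89 | 11% |
| 0.7 | 0.92 | 8% |
| 0.8 | 0.95 | 5% |

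**6. The normality test.** Exactly normal scores were rounded to whole points (N = 234) and tested at 0.05. From SD 5 down to SD 2.5, the uncorrected Kolmogorov-Smirnov test rejected in about 4% to 84% of samples, and the Lilliefors form in about 77% to 100%. These figures carry simulation error of a few percentage points. The underlying variable is normal here, so every rejection beyond the nominal rate comes from rounding, which a transformation cannot remove.

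**The case against.** The strongest reply is that the first two faults largely cancel. If main-effect covariates hardly move the primary contrasts, it matters little which ones are picked. This stands. In a null simulation of the planned rule (78 per arm, ten screened covariates of which two were prognostic, about 16% dropout, ρ = 0.6 assumed), type I error over the four interactions was 0.049 to 0.058 with selection and 0.049 to 0.057 without. A reader might infer from the 40 to 64% chance of a spurious flag that the primary test is inflated; nothing supports that.

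It is also fair that the change contrast already removes any time-constant covariate effect and that, under randomisation, the unadjusted contrast is unbiased with complete data. One might infer that failing to adjust biases the result. That would need an actual imbalance in a variable that drives change, and the article gives no evidence of one.

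Nor does the adjustment do literally nothing. The invariance is exact only for complete data in the linear model. It is approximate under dropout, and it does not carry over to the logistic and multinomial models planned for some outcomes.

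On normality, a reader might conclude that the test is bound to reject, or that a transformed result would be uninterpretable and outside the 0.58 planning effect. Rejection depends on the test variant and on an SD that the article does not give. Log and square-root scales can be interpreted. For a rounded-normal score with assumed mean 12 and SD 3.5, a 0.58 SD shift remains 0.56 to 0.57 after common transformations, so power is barely touched.

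Last, covariate detail is often left to an analysis plan. Here, though, the article does not stay silent; it states selection and transformation rules, and these are the ones at fault.

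**Conclusion.** The point holds as a should-fix. As written, the covariate rule selects on chance imbalance, leaves an open list, and enters the result where it does not act on the treatment contrasts: zero effect with complete data, a few hundredths of an SD under the expected dropout. The cost is an unfixed primary model and forgone precision, 5 to 13% of the standard error for assumed correlations of 0.8 to 0.5. Bias or type I error inflation of the primary test is not shown. The reading that covariates enter only as main effects is the natural one, since no covariate-by-time term is described.

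The possible double role of baseline LNST follows from the two differing statements of scope. It is an ambiguity to close, not a stated intention.

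The normality rule can change the scale of the primary outcome because of rounding alone, if LNST is scored in whole points. How often depends on the unknown SD and the test variant. The fault is an unnamed, data-triggered scale, not a demonstrated loss of power or meaning.

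**What to change.** 1. Delete baseline significance testing as a rule for choosing covariates, and delete the open category of other confounders. Baseline tables can stay as description.
2. Before outcome data are examined, name a short list of prognostic covariates from data already collected (for example age, MMSE and chlorpromazine-equivalent dose, described under Recruitment). Enter each with its time interactions so that it acts on the follow-up contrasts.
3. State one treatment of baseline LNST: either a common baseline mean across arms in the repeated-measures model, or an ANCOVA covariate with only the follow-up scores as responses. It should not be both covariate and response.
4. Remove the test-triggered transformation. Analyse LNST in raw points, check model residuals, and give a bootstrap or robust-standard-error analysis as sensitivity.

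The cost is wording in the protocol and analysis plan, a few degrees of freedom and a little more analysis work. No new data are needed. The article reports recruitment as ongoing, so the rules could be fixed before outcomes are examined.

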### Power analysis and sample size

We have calculated the sample size based on the primary outcome as follows: (1) the number of actual pairwise tests to be made for the efficacy of the primary outcome and (2) the two-level modelling approach in the final data analysis, in which the type I error has been adjusted. The statistical efficiency will be ensured using the multivariate analysis of variance (MANOVA) method for multiple group comparison. First, given that video gaming is a fairly novel strategy, we will base the sample size calculation (a priori) [32] on a cognitive-efficacy meta-analysis for patients with schizophrenia [33] showing an overall effect size (ES, Cohen’s *d*) of 0.58 on verbal working memory (a primary outcome). Based on our hypothesis, the primary endpoints will be the effects on verbal working memory after 3 and 6 months of cognitive training group (CogniFit), compared with the other two groups: cognitive training vs. entertainment gaming, cognitive training vs. non-gaming control group, and entertainment gaming vs. non-gaming control group. Four pairwise interactions between the contrast of the two comparisons and the two time points will be tested. For multiple comparison tests of four, for a type I error level of 5% (two-sided), an adjusted significant level should be α/2 = (1- (1–0.05)4) /2 = 0.01274 /2 = 0.0064, and the corresponding z score for a one-tailed test should be 2.49. Given the effect size 0.58, assuming equal sample size of the three groups, with a statistical power of 0.8 and α= 0.01274*,* we will require at least 198 subjects (66 per group at follow-up phase) by applying the equation, 2(Z1-β + Z1-α/2)2 / ES2. According to a meta-analysis [33], the total sample size in previous cognitive training studies was around 50 (range 10–138).

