### Randomisation, allocation concealment and blinding (masking)

After baseline data collection, the trial manager will be notified of new participants. Each participant will be allocated to one of the three arms based on a list of computer-generated random numbers provided by an external clinical trial randomisation service (blocks of 6 consecutive patients, a 1:1:1 ratio). Allocation will be masked to the trial statistician, but it cannot be masked to the research assistants (RAs) who will supervise the gaming sessions and collect follow-up outcome data, or from the study unit staff who will work with the patients. Furthermore, a sub-sample of 150 participants will be recruited for EEG analysis, and 126 participants from our total sample will be randomly selected and assigned to neuroimaging assessment at baseline (fMRI). Again, the participants for neuroimaging assessment will be allocated based on a separate list of computer-generated random numbers provided by an external clinical trial randomisation service (blocks of 6 consecutive patients, a 1:1:1 ratio). The trial manager will inform the RAs the identities of participants allocated to fMRI assessment.

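### The four primary contrasts leave the randomised arms' baseline means free, so they are less precise than a common-baseline or baseline-adjusted contrast from the same data

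*Protocol article*

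**What the plan says.** The main analysis (Protocol article, *Cognitive and clinical outcomes*) is a two-level model with visits nested in patients. LNST at baseline (T1), 3 months (T2) and 6 months (T3) is the response. G2 and G3 indicate the two comparator arms against cognitive training, and T2 and T3 indicate the follow-up visits against baseline. For the intervention effects, "interaction terms between the treatment group indicators, G2 and G3, and time indicators, T2 and T3, will be included in the fixed part". The same section treats the group coefficients as baseline differences and offers a Wald-type test of the baseline difference between G2 and G3. It lists high statistical efficiency as a main advantage of the approach.

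On dependence within patients it says only this: "The within-patient random effects of the outcome measurements will naturally be taken into account by the level two variance in the model".

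Covariates enter if they differ significantly between arms at baseline, or as other possible confounders. Routine adjustment for the baseline LNST score is not planned.

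On timing, *Randomisation, allocation concealment and blinding* says: "After baseline data collection, the trial manager will be notified of new participants". Allocation follows that notice.

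*Power analysis and sample size* sizes the trial for these same interactions: "Four pairwise interactions between the contrast of the two comparisons and the two time points will be tested". It continues: "Given the effect size 0.58, assuming equal sample size of the three groups, with a statistical power of 0.8" and an adjusted alpha of 0.01274, at least 66 per group are needed at follow-up. The formula has no correlation term, and the section does not say whether 0.58 is in units of the cross-sectional SD or of the SD of change.

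**The concern.** In a randomised trial with baseline measured before allocation, any baseline difference between arms is chance. A model that estimates a separate baseline mean for each arm carries that chance difference in full into every group-by-time interaction. A model with one common baseline mean, or one that adjusts for the baseline score, weights it by the observed correlation instead. Both approaches are unbiased under randomisation, and the second is more precise whenever rho is below 1.

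At stake is precision on all four primary contrasts, and on the secondary outcomes that reuse the model, from data the trial already collects. A second question is whether the standard errors depend on an untested covariance assumption, if the single level-two variance is all that the model contains.

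**Working it through.** **Inputs.** From *Power analysis and sample size*: d = 0.58, power 0.80, four tests, adjusted two-sided alpha 0.01274, z = 2.49, 66 per group. Assumed, because the article gives no value: the correlations between visits. Equal outcome variances across visits are also assumed.

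**The plan's own figure.** The Šidák level for four tests is 1 − 0.95^(1/4) = 0.01274, with z = 2.491. The formula gives 2 × (0.8416 + 2.49)² / 0.58² = 65.99, that is 66 per group. Power at 66 is 79.98%. The stated figure reproduces.

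**Variance of the two contrasts**, per arm, in units of the outcome variance:

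- Planned interaction (with complete data, the difference in mean change): 2(1 − rho).
- Common-baseline or baseline-adjusted contrast: 1 − rho².
- Ratio, planned to adjusted: 2(1 − rho) / [(1 − rho)(1 + rho)] = 2/(1 + rho).

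**Power** at 66 per group, if d is in cross-sectional SD units: Φ(0.58 × √(66/(2v)) − 2.491), with v the variance above. At rho 0.4 the planned contrast has v = 1.2, giving Φ(3.042 − 2.491) = 70.9%. The adjusted contrast has v = 0.84, giving Φ(3.635 − 2.491) = 87.4%.

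| rho (assumed) | Variance ratio | Power, planned | Power, adjusted | n per group for 80%, planned | n per group for 80%, adjusted |
|---|---|---|---|---|---|
| 0.3 | 1.54 | 62.7% | 84.2% | 93 | 61 |
| 0.4 | 1.43 | 70.9% | 87.4% | 80 | 56 |
| 0.5 | 1.33 | 80.0% | 91.3% | 67 | 50 |
| 0.7 | 1.18 | 96.5% | 98.5% | 40 | 34 |
| 0.8 | 1.11 | 99.7% | 99.9% | 27 | 24 |

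On this reading of d, the formula matches the planned contrast at rho = 0.5.

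**If d is in change-score SD units instead**, the planned contrast has 80% power at any rho. The adjusted contrast then has v = (1 + rho)/2, and the same formula gives about 93% at rho 0.4 (v = 0.70), 91% at 0.5 (v = 0.75) and 87% at 0.7 (v = 0.85). The gain remains on either reading.

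**Standard errors, if the model has a random intercept alone.** Such a model uses one pooled correlation for all pairs of visits. Take assumed correlations of 0.70 (baseline to 3 months), 0.55 (baseline to 6 months) and 0.70 (3 to 6 months). The pooled value is (0.70 + 0.55 + 0.70)/3 = 0.65.

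- At 6 months, model SE to true SE is √(0.35/0.45) = 0.882. Type I error at nominal 5% is 2[1 − Φ(1.96 × 0.882)] = 8.4%.
- At 3 months the ratio is √(0.35/0.30) = 1.080, and type I error is 3.4%.

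Simulation of 20,000 null trials per pattern, 66 per group, at nominal 5%:

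| Correlations (0–3, 0–6, 3–6 months) | Type I error, 3 months | Type I error, 6 months |
|---|---|---|
| 0.7, 0.7, 0.7 | 5.2% | 4.9% |
| 0.7, 0.5, 0.7 | 3.1% | 9.4% |
| 0.5, 0.5, 0.8 | 8.1% | 7.9% |

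The standard errors are right when variances and correlations are equal. Otherwise the size and direction of the error depend on the pattern.

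**The case against.** The planned model is valid and conventional. Group, time and interaction terms with free baseline means give unbiased effects under randomisation, so this is a matter of efficiency and not of error. That stands. It does not remove the loss, which applies at every rho below 1 and can be avoided at almost no cost. The article itself puts efficiency forward as a reason for the model. The covariate rule is no substitute, because it brings in baseline variables only after a significant imbalance or as unspecified confounders. If baseline LNST met that rule, it would be both response and covariate in one model.

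A reader might go further in three ways that the article does not support.

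- *Baseline is thrown away.* It is not. The change contrast uses it with a coefficient of 1. What is lost is the gap to the best weight, which is small when rho is high.
- *The trial is underpowered.* This is not shown. If d is in cross-sectional SD units, the stated 80% is met at rho of about 0.5 or more. If d is in change-score SD units, it is met at any rho.
- *The standard errors are wrong.* A random intercept alone is the plain reading of a single level-two variance, but it is an inference. The article excludes no richer structure, and an analysis plan that is not shown may specify one. Even on the plain reading, the standard errors fail only if variances or correlations differ between visits.

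It is also fair to object that a common baseline mean should not be imposed everywhere. The footnote to Table 1 calls the EEG group a convenience sample, and the article does not show that its members are chosen before allocation. That limits the remedy for EEG but does not touch the primary outcome.

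**Conclusion.** The point holds as one of efficiency. The fixed part of the primary model is explicit, and it gives each of the four primary contrasts a variance 2/(1 + rho) times what the same data could deliver: 43% larger at rho 0.4, 33% at 0.5, 18% at 0.7 and 11% at 0.8. This rests on randomisation after baseline, which the article states, and on complete data with equal variances across visits, which is assumed. The power cost is material at rho of 0.5 or below and negligible at 0.7 or above if d is in cross-sectional SD units. Since the article gives neither rho nor the SD behind d, no single power figure can be claimed.

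The covariance point is conditional and serves only as a reason for a safeguard. For two-visit outcomes with complete data there is no three-visit correlation pattern to misstate, so only the efficiency point applies to them.

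**What to change.** - **LNST and the other continuous three-visit outcomes:** keep T2, T3 and their interactions with G2 and G3, and drop the G2 and G3 main effects so that all arms share one baseline mean. Alternatively, model the two follow-up visits with the baseline score as a covariate. Drop the baseline test of G2 against G3.
- **Safeguard:** state an unstructured 3×3 within-patient covariance with Kenward-Roger degrees of freedom, so that the standard errors do not rest on equal correlations.
- **Sample-size text:** say which SD the 0.58 refers to and, if it is the cross-sectional SD, which rho is assumed.
- **EEG:** adjust for the baseline value as a covariate and do not constrain the baseline means.
- **MRI:** use the common baseline mean only if the subsample is drawn independently of arm. Otherwise adjust for baseline as for EEG.

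The cost is model wording and code, plus four extra variance parameters (six for the unstructured matrix against two for a random intercept with residual). No further patients or measurements are needed, since LNST is already scheduled at baseline, 3 months and 6 months.
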